### sPLA2 and ARDS

A wide body of literature suggests a role for sPLA2 in the development of ARDS and acute lung injury (ALI), its milder form. sPLA2 interferes with the surfactant activity and so reduces compliance [4-6]. sPLA2 starts a vicious cycle in which it damages the surfactant; since some surfactant components have their own inhibitory effect on sPLA2 activity and expression [7,8], the sPLA2-induced surfactant damage reduces this inhibition and thus the enzyme is able to further catabolize the surfactant phospholipids [4]. Thus, sPLA2 facilitates the action of other injurious agents against the lung epithelium, leading to further surfactant damage, alveolar collapse and respiratory impairment [4]. This process is also linked to the lung tissue inflammation, since TNFα and some other pro-inflammatory cytokines are strong sPLA2 inductors throughout the regulation of NFkB nuclear transcription factor [4,7,8]. Moreover, sPLA2 itself starts the inflammatory cascade, since it is the first step in the biochemical pathway leading to the production of arachidonic acid derivatives [9]. Inflammation may further inactivate surfactant, contributing to the above-described vicious cycle [4-6]. sPLA2 activity is raised in broncho-alveolar lavage fluid (BALF) in animal models of ARDS and in adult patients and this correlates with the clinical severity and mortality [4,5,8,10]. We recently found raised enzyme levels in post-neonatal ARDS, similarly to the adult findings [11]. Moreover, respiratory syncytial virus (RSV) infection seems to cause a more severe ARDS because of the sPLA2 over-expression, triggered by the RSV itself [12]. Consistently, transgenic animals defective for the CCSP gene, experience higher inflammation and mucous production, when infected by RSV [13].

In animal models, the administration of sPLA2 inhibitors reduced lung inflammation and improved both compliance and oxygenation, especially if the inhibitor is administered early during the injury development [8,14]. Similarly, the inhibitor was able to reduce sPLA2 activity in BALF of patients with iRDS, IRRF, MAS and post-neonatal ARDS [15].

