### sPLA2 and iRDS

The importance of surfactant is well known in neonatal critical care. An inadequate surfactant production is the pivotal cause of hyaline membrane disease, also called infant respiratory distress syndrome (iRDS), the most frequent respiratory disease of preterm infants [16]. Although exogenous surfactant administration is curative in many preterm infants, long-term respiratory sequels are still a significant problem in this population, with 20% of the surviving preterm babies affected by BPD [17]. Moreover, the tiniest babies born at the limit of viability often require multiple surfactant administrations. Many of these very preterm deliveries are associated with infections and chorioamnionitis [18]. In these cases, inflammation lengthens the lung injury, decreasing the usefulness of exogenous surfactant and damaging the lung tissue [18]. In such situation, sPLA2 is likely to play a crucial role: we found increased sPLA2 levels in babies with iRDS comparing to normal term neonates [19]. sPLA2 was found to increase foetal neutrophil migration and so to enhance lung tissue inflammation [20]. Babies with higher sPLA2 activity are likely to be the ones needing repeated surfactant administrations and they are at higher risk for chronic lung disease.

Some authors recently tried to administer CCSP to preterm neonates. CCSP is a natural inhibitor of sPLA2 in the lung [21,22]. This drug has been given endotracheally together with surfactant [21] achieving a significant reduction in lung tissue inflammation. Similar results in terms of inflammatory markers and lung function have been obtained in animal models of iRDS and MAS [23-25].

Other authors have proposed the same approach with endotracheally administered budesonide, vehicled by surfactant [26]. Budesonide inhibits sPLA2 and has been associated with a decrease in the release of sPLA2-induced pro-inflammatory cytokines [27]. Surfactant is the cornerstone of iRDS therapy and the sPLA2 inhibition could theoretically protect it, reducing the need for repeated doses and improving the long-term respiratory outcome.

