#### 1) clinical phase

##### Enrolment

The following group of patients will be identified: iRDS, IRRF, MAS, ARDS-ALI. To be enrolled in a group babies must fulfil all the following inclusion criteria:

A. Preterm neonates (gestational age ≤ 37 sett) with iRDS

*C-Reactive protein (CRP) < 10 mg/L or procalcitonin (PCT) < 0.6 ng/mL in the first 72 hours of life; Chest-X-rays typical for iRDS; no clinical signs of sepsis; need for mechanical ventilation*.

B. Infants and neonates with IRRF (regardless of the age)

***B1. Early IRRF. Neonates from mother with vaginal or urine positive cultures***. *Respiratory distress signs and CRP > 10 mg/L *[52]*or PCT > 0.6 ng/mL *[53]*in the first 72 hours of life; clinical signs of sepsis or blood/BALF positive culture; need for mechanical ventilation*.

***B2. Late IRRF***. *Neonates with respiratory distress signs beyond the first 72 hours of life or infants, irrespectively of the age and CRP > 10 mg/L *[52]*or PCT > 0.6 ng/mL *[53]; *clinical signs of sepsis or blood/BALF positive culture; need for mechanical ventilation*.

C. Neonates with MAS

*Neonates with meconium stained and thick amniotic fluid who required broncho-aspiration following Neonatal Resuscitation Program guidelines*[54]. *Continuous need for mechanical ventilation at 15 minutes of life. Chest-X rays typical for MAS*.

**D. Infants with ARDS-ALI **[55]

*Infants beyond neonatal age (> 30 days of life) and < 1 year of age under mechanical ventilation and having PaO_2_/FiO_2 _ratio < 200 (ARDS) or < 300 (ALI), chest-X rays typical for ARDS-ALI, acute onset of the respiratory distress and no cardiogenic oedema/increase in left atrial pressure*.

A control group has also been previewed, as follows:

E. Infants and neonates without respiratory diseases (NLD: No lung disease)

*Patients ventilated for non-pulmonary reasons (e.g.: anaesthesia, central nervous system diseases), PaO_2_/FiO_2 _ratio > 300 or FiO_2 _= 0.21, negative CRP and PCT, normal chest-X rays and chest clinical examination*.

A careful revision of the clinical characteristics will be done for each patient at the moment of discharge (or death). This will be done in each centre to ensure the appropriateness of diagnosis and internal validity.

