##### Statistics and sample size

Data will be tested for normality and then analyzed with parametric or non-parametric procedures, as appropriate. Accordingly, univariate analysis using Student and analysis of variance or Mann-Whitney, Wilcoxon, Kruskal-Wallis and Friedman tests will be performed. Some laboratory data will be subjected to correlation analysis with clinical findings, using Pearson's, Spearman's or Kendall's technique, according to data characteristics.

Subsequently, if needed, significant results will be subjected to multiple curve estimation procedure [66] and/or multivariate analysis according to data characteristics and the results of the univariate analyses. The genetic data will be analyzed using χ^2 ^test for the Hardy-Weinberg equilibrium of alleles at the individual loci. The association between genotypes and clinical data will be tested with χ^2^- or Fisher test and then with logistic regression or analysis of co-variance, as appropriate [67]. All statistical analyses will be performed by the project coordinators, who have a long experience and formal training in biostatistics.

Despite a formal sample size calculation is not warranted, based on the available data [5,11,19], we previewed a convenience sample size, as follows: 50-60 preterm infants affected by iRDS, with at least 20 receiving a second surfactant dose; for ARDS and IRRF groups 20 patients will be also convenient, while 10 control neonates or infants will be considered. These sample size have been checked for power regarding the correlation between sPLA2 activity and two selected clinical variables (using Power and Precision demo rel. 3.2 [68]). Given α-error of 0.05 and a correlation coefficient (*r*) ≥ 0.6 and ≥ 0.85 [5,11,19] for the respiratory compliance and the PaO_2_/FiO_2 _ratio, respectively, the power resulted > 80% in both cases.

The study is supposed to last 12-18 months for the enrolment phase in each collaborating centre, and 3-6 months for the laboratory phase at the coordinating centre.

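### The ten lung-disease-free controls have no age or gestation requirement, yet they serve both newborn groups and ARDS-ALI infants older than 30 days, so a disease-versus-control difference may partly reflect age

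*Protocol article*

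**What the plan says.** The Enrolment section ties three of the four disease groups to an age:

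- Group A: "Preterm neonates (gestational age ≤ 37 sett) with iRDS".
- Group C: neonates with MAS, still needing ventilation at 15 minutes of life.
- Group D (ARDS-ALI): "Infants beyond neonatal age (> 30 days of life) and < 1 year of age under mechanical ventilation".
- Group B (IRRF) is open to any age.

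One comparator without lung disease is then introduced ("A control group has also been previewed, as follows") and headed "E. Infants and neonates without respiratory diseases (NLD: No lung disease". Its criteria cover the reason for ventilation, oxygenation, CRP and PCT, chest X-ray and chest examination. None concerns postnatal age or gestation, and the upper limit of 1 year given to group D is not repeated.

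Statistics and sample size gives 50-60 iRDS patients and 20 for ARDS and IRRF (read here as 20 each). For the comparator it says "while 10 control neonates or infants will be considered". Groups are compared with unadjusted univariate tests. Multivariate work follows only where judged necessary and only for significant results, and no covariate is named. Gestational age or age in months is among the recorded data.

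**The concern.** The study hypothesis includes a role for sPLA2 or its modulators in pathogenesis. Group E is the only planned group free of lung disease, so it is the natural reference for that part of the hypothesis. Comparing disease groups with each other would not avoid the age problem, because newborn iRDS and MAS patients are separated in age from ARDS-ALI patients by definition.

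A control several months old may be a poor reference for a preterm newborn, and a newborn control may be a poor one for an infant with ARDS. If marker levels differ between these ages for reasons unrelated to lung disease, an off-age control pool shifts the disease-versus-control difference, and an unadjusted test attributes the shift to disease. Controls never enrolled in the needed age band cannot be supplied at analysis.

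**Working it through.** **1. The plan's own figure.** The article states power above 80% for correlations of r ≥ 0.6 and r ≥ 0.85 at α = 0.05. Using Φ(atanh(r)·√(n−3) − 1.96) with n = 20:

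- r = 0.6: Φ(0.693 × 4.123 − 1.96) = 81.5%.
- r = 0.85: 99.9%.

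The statement reproduces. It concerns correlations within a disease group, which need no controls. No power is stated for any disease-versus-control contrast.

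**2. Inputs for the contrast.** Cases: 55 iRDS (midpoint of 50-60) or 20 ARDS. Controls: 10. No number is given for MAS, so none is computed. The article gives no marker values by age in lung-healthy children, so the age shift a is an assumption, taken as 0.3, 0.5 and 0.8 SD. The true disease effect is set to zero.

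**3. Bias.** If k of the 10 controls are off-age, the expected difference is a·k/10. For a = 0.5 SD this is 0.25 SD with k = 5 and 0.5 SD with k = 10.

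**4. False-positive rate.** Two-sided 5% t-test, Mann-Whitney in brackets; simulation with normal outcomes, SD 1, 6,000 replicates per cell:

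| Comparison | Off-age controls | 0.3 SD | 0.5 SD | 0.8 SD |
|---|---|---|---|---|
| 55 iRDS v 10 | 5 | 7% (6%) | 10% (9%) | 20% (17%) |
| 55 iRDS v 10 | 10 | 14% (13%) | 29% (27%) | 63% (60%) |
| 20 ARDS v 10 | 5 | 7% (6%) | 9% (8%) | 16% (13%) |
| 20 ARDS v 10 | 10 | 11% (10%) | 25% (21%) | 52% (47%) |

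With no off-age controls the rates were 4% to 5%. Reruns of the t-test agreed to within about one percentage point. The two rows with 10 off-age controls are alternatives: on a neonate-infant difference, a pool wholly off-age for iRDS is wholly on-age for ARDS, and the reverse.

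**5. What age-matching costs.** Difference detectable with 80% power, two-sided 5%, from the noncentral t:

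- iRDS: 55 v 10 = 0.98 SD; 55 v 5 = 1.33 SD.
- ARDS: 20 v 10 = 1.12 SD; 20 v 5 = 1.46 SD.

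**6. Pooled or age-matched contrast.** With five controls per band and 55 iRDS cases, mean squared error in SD² units is:

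- Pooled: (a/2)² + 1/10 + 1/55, which is 0.14, 0.18 and 0.28 at a = 0.3, 0.5 and 0.8.
- Age-matched: 1/5 + 1/55 = 0.22 at any a.

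The two are equal when (a/2)² = 1/10, that is a = 0.63 SD. Below that the pooled contrast is the more accurate, and above it the age-matched one is. Neither is better throughout the assumed range.

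**The case against.** **The age effect is not in the article.** This stands. The article says of surfactant and sPLA2 that "since some surfactant components have their own inhibitory effect on sPLA2 activity and expression [7,8", and it names inadequate surfactant production as the cause of iRDS. A reader might infer that the protocol's own mechanism makes lung-healthy neonates and infants differ. It does not say so: the first statement does not mention age and the second describes a disease. The concern is conditional on an age effect.

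**The large figures are extreme cells.** This also stands. A half-and-half pool at 0.3 to 0.5 SD gives 6% to 10% across both tests. The figures above 50% with the t-test need 0.8 SD and all ten controls from the wrong band, which can hold for only one of iRDS and ARDS.

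**Adjustment may help.** Partly right. Age is recorded and multivariate analysis is allowed. A reader might infer that adjustment can never repair the problem, but that holds only for a pool drawn wholly from the other band. In a mixed pool some adjustment is possible, although the plan makes it optional and restricts it to significant results.

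**The control contrast is not declared the main analysis.** True. None of the four listed aims mentions controls, so the study as a whole does not rest on group E.

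**The earlier iRDS study.** The article reports that "we found increased sPLA2 levels in babies with iRDS comparing to normal term neonates [19". A reader might infer that the control definition has since been widened. The article does not support this: the sample size also cites a post-neonatal ARDS study whose controls are not described, and including infants fits a study that enrols group D.

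**Strict non-overlap.** It applies to newborn iRDS and MAS against ARDS-ALI. iRDS and MAS are both neonatal, MAS has no gestation limit, and IRRF spans all ages.

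**A full protocol may hold quotas.** Possibly. But the article itself states the eligibility and size of group E, and as stated they allow any age mix.

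**Conclusion.** The point holds as a conditional design weakness. One pool of ten controls with no age or gestation criterion is the only lung-disease-free comparator for newborn groups and for a group that starts after 30 days of life. If sPLA2 or its modulators vary with age, part of a disease-versus-control difference may be age.

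Under an assumed shift of 0.3 to 0.8 SD, normal outcomes and no disease effect, the t-test error rate rises from 5% to about 7-20% with half the controls off-age. It rises to about 11-63% for whichever of iRDS or ARDS has all ten off-age. The documents do not show that such a bias will occur. The within-disease correlations and their stated power are untouched.

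The change is worth making before enrolment, since an age band left empty cannot be filled afterwards.

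**What to change.** Keep ten controls and set a quota by age band, for example five at 30 days or less (preterm where available) and five over 30 days and under 1 year. Add the under-1-year limit to group E.

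Report each disease-versus-control contrast against the age-matched controls alongside the contrast with all ten, and draw a pathogenesis conclusion only where the two agree. Define agreement beforehand on the direction and size of the estimates. State that if the neonatal controls are born at term, the iRDS contrast cannot separate disease from prematurity; the quota does not remove that limit.

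Cost: one enrolment sentence, a short analysis statement and a small recruitment constraint, with no extra patients or procedures and no new data items. The age-matched contrast is imprecise, as step 5 of the working shows, which is why it should accompany the pooled contrast and not replace it. No power stated in the plan is lost.

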## Ethical considerations

The protocol and consent form have been approved by the Ethical Committee of the University Hospital "*A.Gemelli*" at the Catholic University of the Sacred Heart (Rome, Italy) as coordinating centre. Local ethical boards in each collaborating centre have also approved the protocol.

The participation to the study will not change in any way the routine clinical assistance previewed for every patient. Furthermore, the participation to the study will respect all the local Regulations about safety procedures and the privacy. Informed consent will be given by parents or tutors of each baby, before the enrolment in the study.

## Publication policy

Study results will be presented to each investigator by teleconference and/or e-mail. If possible a meeting in occasion of one of the major congresses in the field of Paediatrics or Critical Care (like the European Society for Paediatric Research or European Society for Paediatric and Neonatal Intensive Care Congresses) will be organised. Data will be also presented at these meetings and the subsequent manuscripts will be circulated between all investigators for revision. All resulting manuscripts will be authored by the project coordinators and by the group authorship (SSPP: Study group on Secretory Phospholipase in Paediatrics).

## Discussion

This study, thanks to its multicenter design, will clarify the role(s) of sPLA2 and its pathway modulators in several paediatric and neonatal forms of lung injury. In fact, enough evidence is available to indicate sPLA2, or at least some of its subtypes, as a key point in the pathophysiology of certain critical respiratory diseases. Inflammation is a complex process and is essential in many of these conditions: sPLA2 might be the main crossroad between inflammation and surfactant catabolism. Since this latter is surely an important component of some clinical situations, sPLA2 is worth to be studied in its metabolic and genetic issues, trying to correlate them to the clinical pictures.

Given the peculiarity of such diseases and the relative rarity of some of them, only a multicentre design will be able to clarify this field. The purpose is not free from practical consequences, as several sPLA2 inhibitors are now available or under advanced development [69]. Many drugs are already used in respiratory critical care [70] but sPLA2 blockade might represent a new anti-inflammatory therapy and a novel approach to protect surfactant or spare it, improving alveolar stability, lung mechanics and gas exchange.

The establishment of a net of centres involved in clinical research, along with the support of bench investigators, will help in understanding this field and in building future randomised interventional studies.

## List of abbreviations

sPLA2: secretory phospholipase A2; CCSP: Clara cell secretory protein; SP-A: Surfactant protein A; ARDS: acute respiratory distress syndrome; ALI: acute lung injury; BALF: broncho-alveolar lavage fluids; iRDS: infant respiratory distress syndrome or hyaline membrane disease; BPD: broncho-pulmonary dysplasia; MAS: meconium aspiration syndrome; IRRF: infection related respiratory failure; RSV: respiratory sincytial virus; SSPP: Study group on Secretory Phospholipase in Pediatrics; CRP: C-Reactive protein; PCT: procalcitonin; Pāw: mean airway pressure; DCO_2_: Alveolar ventilation estimation during high frequency oscillatory ventilation; cPLA2: cytosolic phospholipase; SNP: single nucleotide polymorphisms.

## Footnote

^§ ^Compliance measurement depends on the type of ventilator. Those with the end-expiratory occlusion will provide a static measure, otherwise a dynamic measurement will be done using the hot-wire anemometer flow sensor. In that case, to increase the measurement accuracy, the spontaneous breathing must be temporarily avoided, gas leaks must be < 5% and stable respiratory conditions with minimal airway secretions must be achieved. Conditions and technique for this measurement have been described in details elsewhere [15].
